## **Impact of Heartfulness meditation practices compared to the Gratitude practice on compassion fatigue, compassion satisfaction, burnout and work engagement for healthcare professionals across United States: Randomized Trial**

### **Background**

While involved in the noble profession of helping fellow human beings, healthcare workers are exposed to a challenging work environment where they encounter distressed patients and families. Compassion and empathy are expected of all healthcare professionals though this constant demand can become overwhelming depending on the work environment, patient population, and workload. *Compassion satisfaction* is a positive, altruistic quality that describes self-appreciation while caring for and helping others. *Compassion fatigue* is the psycho-emotional distress that originates from long-term self-sacrifice coupled with prolonged exposure to difficult situations. There are two parts of compassion fatigue. The first part concerns things such as exhaustion, frustration, anger, and depression typical of burnout. *Secondary Traumatic Stress* is a negative feeling driven by fear and work-related trauma. Whereas compassion fatigue is rapid in onset, burnout is a slowly progressing disorder usually seen in a burdensome organizational environment.

Nurses are especially prone to reduced compassion satisfaction, higher compassion fatigue, and burnout when they experience continual physical and psychological stress originating from the care of patients, most of whom are seriously ill, and many of whom are traumatized. Compassion fatigue and burnout suffered by nurses are well described in the literature. A meta-analysis of 21 studies demonstrated the prevalence rates of compassion satisfaction, compassion fatigue, and burnout were 47.55%, 52.55%, and 51.98%, respectively, among the nurses of different areas. The function of a healthcare system depends on the tight integration and interdependency of physicians, nurses, and allied healthcare professions. Allied healthcare workers such as respiratory therapists, physical, occupational, and speech therapists are also expected to be exposed to similar work-related stress while caring for their patients, even though literature is lacking in this aspect. The health administrators strive to improve the mental wellbeing of their workforce as it is essential to provide quality of care and improve patient satisfaction. Strategies such as optimal workload assignment, collegial work environment, continuing education, leadership are critical general interventions to help the healthcare workforce. Every individual tends to cope differently with the stressful work environment or challenging patient or family interactions, depending on one's inner emotional state. A healthcare administration can potentially help their healthcare workers by providing tools of self-care to better cope with day-to-day stressors associated with providing care to patients and enhance resilience.

Relaxation techniques and meditation practices have been shown to reduce compassion fatigue and burnout among healthcare providers. These studies were limited by lack of randomization or lack of control group. The heartfulness practice comprises a morning session focusing on relaxation and meditation, an evening rejuvenation session that involves removing emotional impressions of the day, and a session at night for a deeper connection with oneself involving a

short meditation session before sleep. In addition, trainer-guided sessions are also offered. Heartfulness meditation practice has been shown to decrease loneliness & improve sleep; and reduce burnout in healthcare workers.

The American Nurses Foundation and the Greater Good Science Center (GGSC) at the University of California, Berkeley, have developed a Gratitude Practice for Nurses Toolkit to support nurses' social and emotional wellbeing. It is unclear if gratitude improves compassion fatigue and burnout and improves mental wellbeing, especially for healthcare workers, including nurses, as limited research data from randomized studies is available in this population.

Work engagement is the assumed opposite of burnout. Contrary to those who suffer from burnout, engaged employees have a sense of energetic and effective connection with their work activities and they see themselves as able to deal well with the demands of their job. It would be essential to measure work engagement among healthcare workers.

This study will investigate whether heartfulness meditation practice leads to measurable changes in compassion fatigue, compassion satisfaction and burnout as well as improvement in work engagement among the healthcare providers across US compared to Gratitude practice.

### **The objectives of the study**

The primary objective of this study is to investigate an impact of a virtual, heart-based meditation program (Heartfulness practice) guided through a Heartfulness trainer compared with a self-motivated Gratitude practice for nurses designed by the American Nurses Foundation and the Greater Good Science Center (GGSC) at the University of California, Berkeley on the burden of compassion fatigue and burnout among the nurses and allied healthcare providers.

The secondary objective is to investigate if a virtual, Heartfulness practice guided through a Heartfulness trainer results in a sustained reduction in compassion fatigue and burnout as well as improvement in work engagement among the healthcare providers.

### **Study Population and Recruitment Methods**

We would like to implement an adaptive recruitment strategy to recruit a higher number of participants in the intervention group expecting a high attrition rate observed in previous studies where meditation practice was employed as an intervention. We would like to recruit 200 participants in the intervention group and 100 participants in the control group. Willing volunteers will be consented to, enrolled, and data will be collected and analyzed.

### **Inclusion and Exclusion Criteria**

Inclusion criteria:

1. Adults above 18 years of age willing to participate in the study
2. Any healthcare worker involved in direct patient care at any healthcare facility within United States

3. Requires basic knowledge of the Internet and ability to follow instructions regarding email communications as well as accessing video conferences

Exclusion criteria:

1. Individuals less than 18 years of age
2. Participants with a history of meditation practice ( $\geq 100$  hours of meditation) will be excluded from the study to avoid participant bias

Disclaimer: Any person under medical care for depression or other mental health conditions is encouraged not to participate or only participate after discussion with his/her healthcare provider so that the study participation does not interfere with current treatment.

### **Study design**

This study will be randomized control trial where the participants will be randomly assigned to the Heartfulness meditation group (Intervention group) or the Gratitude practice group (Control group). All participants will be requested to fill out professional quality of life (ProQOL) survey and the “Participants’ Details” (including age, gender, work designation, years of experience, level of education, primary patient population etc.) forms before randomization. Participants will be subjected to computerized randomization to intervention group or Heartfulness meditation group and control group or the Gratitude practice group. All participants were requested to complete the professional quality of life (ProQOL) and , Work engagement scale at the baseline and at the end of 6-weeks, which will complete the first phase of the study.

If equal or more than 20 participants are willing to participate, we will continue with a second phase of the study where the trainer guided Heartfulness program will continue for six months to assess the long-term impact of Heartfulness practice on compassion fatigue and burnout. Email communication will be sent to all participants at the end of 6 weeks, asking for voluntary participation. Participants who volunteer for the second phase of the study will be asked to complete a same survey at three months and six months. Participants in Gratitude practice group will also be asked to complete the survey at three and six months after completion of study.

All participants in both groups will be provided with information, including recorded video presentations for Heartfulness meditation practice and the Gratitude practice, at the end of 6 weeks.

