### Gratitude practice group

All participants in the Gratitude practice group will be invited for an orientation session on the aspects of the study and review of the toolkit for cultivating the practice of gratitude in nursing. This program created by the American Nurses Foundation and the Greater Good Science Center (GGSC) at the University of California, Berkeley, is designed to support nurses' social and emotional wellbeing. This toolkit is based on scientific research revealing the many benefits of gratitude. This toolkit provides different ways for individuals to express gratitude during their daily interactions and work environment, such as writing a gratitude letter, taking a savoring walk, a few minutes before and after each patient encounter, during staff huddle, etc. Participants would have an opportunity to participate in a 21-days gratitude challenge by registering on [www.Thnx.org](http://www.Thnx.org) if offered during the study period. All participants will be sent an email once a week during the study period to provide a gentle reminder to practice gratitude. Participants will be asked to attend an orientation session via Zoom about Gratitude Science for 1 hour. If the participant cannot attend the meeting, they can review the recorded video for information. Participants will be provided with information to access podcast each week on gratitude practice during the 6-week study period. Tool kit available at: [https://ggsc.berkeley.edu/gratitudeforurses?\\_ga=2.59198189.1166833940.1621437217-1764624032.1620078854](https://ggsc.berkeley.edu/gratitudeforurses?_ga=2.59198189.1166833940.1621437217-1764624032.1620078854). Subjects in the control group will also complete the ProQOL-5 at the beginning and end of the six weeks and after 3 & 6 months unless they start practicing Heartfulness meditation.

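### The 3- and 6-month surveys are tied to volunteering in the Heartfulness arm and to not switching in the Gratitude arm, so the data on sustained benefit are filtered after randomisation by a different rule in each arm

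*Protocol*

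**What the plan says.** The secondary objective (The objectives of the study) asks whether trainer-guided Heartfulness "results in a sustained reduction in compassion fatigue and burnout as well as improvement in work engagement among the healthcare providers". Unlike the primary objective, it names no comparator.

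The Study design section sets up the long-term follow-up in four steps:

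- Invitation: "Email communication will be sent to all participants at the end of 6 weeks, asking for voluntary participation".
- Condition for going ahead: "If equal or more than 20 participants are willing to participate, we will continue with a second phase of the study".
- Survey for those who opt in: "Participants who volunteer for the second phase of the study will be asked to complete a same survey at three months and six months".
- Survey for controls: "Participants in Gratitude practice group will also be asked to complete the survey at three and six months after completion of study".

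The Gratitude practice group section adds an exception for controls, who complete the ProQOL-5 "after 3 & 6 months unless they start practicing Heartfulness meditation". At week 6 both arms also receive the materials for both practices (Study design).

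The Measure section points another way. It addresses the qualitative questions to all participants, as part of the survey at 6 weeks, 3 months and 6 months.

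On numbers, Study Population and Recruitment Methods says: "We would like to recruit 200 participants in the intervention group and 100 participants in the control group". The unequal split is explained as "expecting a high attrition rate observed in previous studies where meditation practice was employed as an intervention", with no rate given.

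**The concern.** Volunteering takes place after randomisation and after six weeks of practice, when participants know how the practice has worked for them. If the later survey goes only to those who volunteer, whether a Heartfulness participant is measured depends on something plausibly related to the outcome. In the Gratitude arm, measurement depends on a different behaviour, namely not taking up Heartfulness. Random assignment then no longer protects a comparison of the arms at 3 or 6 months.

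This is a rule about data collection, so later analysis cannot fully repair it: the outcomes of participants who were never asked do not exist. Sustained benefit is the protocol's only stated secondary objective, and the Background criticises earlier studies for lacking randomisation or a control group. The second phase, as written, brings that weakness back.

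**Working it through.** **Who is surveyed at 3 and 6 months, by section**

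| Group at week 6 | Study design | Gratitude practice group | Measure (qualitative questions) |
|---|---|---|---|
| Heartfulness, volunteers | yes | – | yes |
| Heartfulness, declines | not provided for | – | yes |
| Gratitude, does not switch | yes | yes | yes |
| Gratitude, starts Heartfulness | yes | no | yes |

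The second and fourth rows conflict between sections. The clock may differ too: volunteers are surveyed at three and six months, controls at three and six months after completing the study.

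**Two readings of the secondary objective.** With no comparator, the result is a before-after change in people who chose to continue. With the Gratitude arm as comparator, it is a comparison of groups selected by different post-randomisation rules.

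**Size: illustration only.** The protocol gives no power, SD, effect size or volunteering rate, so there is no figure to reproduce. All of the following are assumed:

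- no true effect; outcomes at baseline, week 6 and follow-up normal with SD 1 and pairwise correlation r = 0.6;
- odds of volunteering multiplied by 1.6 to 2.7 per SD of week-6 improvement (logistic model);
- a share p of the 200 volunteers, so n = 200p, against 100 unselected controls; two-sided 5% test.

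The bias b is the simulated mean advantage of volunteers (2 million draws). The standard errors are

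- change score: SE = √[2(1 − r)(1/n + 1/100)];
- baseline-adjusted: SE = √[(1 − r²)(1/n + 1/100)].

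The false-positive rate is Φ(b/SE − 1.96) + Φ(−b/SE − 1.96).

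For p = 25%, n = 50:

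- Change score: SE = √(0.8 × 0.03) = 0.155. With b = 0.15, b/SE = 0.97 and the rate is 16%. With b = 0.285, b/SE = 1.84 and the rate is 45%.
- Adjusted: SE = √(0.64 × 0.03) = 0.139. With b = 0.09, b/SE = 0.65 and the rate is 10%. With b = 0.17, b/SE = 1.22 and the rate is 23%.

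| Volunteering | n | Change score | Baseline-adjusted |
|---|---|---|---|
| 10% | 20 | 13–38% | 9–20% |
| 25% | 50 | 16–45% | 10–23% |
| 50% | 100 | 12–30% | 8–17% |
| 75% | 150 | 7–13% | 6–9% |

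The 25% row is the worst of the four. A cruder model gives a much wider range. It takes b = r′φ(z)/p, where z is the 1 − p normal quantile and r′ (0.1 to 0.5) is the correlation between the tendency to opt in and the outcome. Its rates run from 6% to 98% over the same volunteering shares. The size is therefore not determinable from the documents. Dropping controls who switch would add a further bias of unknown direction.

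**Precision.** The effect detectable with 80% power, two-sided 5%, is 2.80 × √(1/n₁ + 1/n₂) SD without baseline adjustment:

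- 20 vs 100: 2.80 × √0.06 = 0.69 SD;
- 200 vs 100: 2.80 × √0.015 = 0.34 SD, only if everyone responds;
- 100 vs 50 (assumed half responding): 2.80 × √0.03 = 0.485 SD.

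Baseline adjustment with r = 0.6 multiplies each by √(1 − 0.36) = 0.8, so the first two become 0.55 and 0.27 SD.

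**The case against.** Several points on the other side have force.

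- **The Measure section addresses all participants.** A reader of Study design alone might infer that decliners certainly receive no later survey. That section assigns the survey to volunteers but does not expressly exclude others. What can be said is that the sections conflict. The Measure sentence concerns the qualitative questions and does not clearly extend the ProQOL and UWES to decliners.
- **No between-arm test at 3 or 6 months is specified.** This stands. Surveying the controls makes such a comparison plausible, but it is an inference. The false-positive rates matter only if that test is run and read as evidence of effect. Without it, what remains is an uncontrolled change, which is no stronger.
- **The trigger of 20 need not be 10% of the Heartfulness arm.** The invitation goes to everyone, so the 20 may not all be Heartfulness participants, and 200 is a recruitment target with attrition expected.
- **The direction of bias is assumed.** Participants who are still distressed might be the ones who continue.
- **Attrition would filter the sample anyway.** True, but not answering a survey differs from not being sent one. Asking everyone permits an analysis as randomised and an examination of missing data.
- **An SAP could label the phase descriptive.** It could, and that would limit the inferential harm. It could not recover outcomes that were never collected.

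**Conclusion.** The point holds for the long-term follow-up. Under Study design and the Gratitude practice group section, data on sustained benefit are filtered after randomisation by different rules in the two arms. They could show a benefit where none exists if those who improved are likelier to continue. The illustrated inflation of a nominal 5% test rests wholly on assumed correlation, selection strength, volunteering share and unselected controls. It shows that the problem can be material, not how large it is here.

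Two stronger conclusions are tempting and are not supported. One is that the results would show a sustained reduction regardless of the truth: even the worst case in the main illustration is non-significant more than half the time. The other is that the secondary objective cannot be addressed at all: a descriptive account of continuers remains possible, though weak. The primary comparison at 6 weeks is untouched. The matter needs settling before participants reach week 6, since follow-up not requested then may not be recoverable.

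**What to change.** - Send the 3- and 6-month ProQOL and UWES survey to every randomised participant in both arms, at the same time points counted from the same origin, whether or not they continue or switch practice.
- Delete the exception in the Gratitude practice group section as far as it concerns the survey, and reconcile Study design with Measure on who receives it.
- Analyse by randomised arm, and report results in continuers as descriptive only.
- State whether the secondary objective is a comparison with Gratitude.
- Let the 20-volunteer rule decide only whether guided sessions continue, not whether follow-up is collected.

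The cost is protocol wording, two more Qualtrics mailings to the full list, and consent wording if needed. The response rate is likely to be lower among those who stopped practising, so the 0.34 SD for full response should not be promised.

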### **Recruitment**

This study will be open to all healthcare professionals involved in direct patient care in any healthcare institution across United States. Principal investigator and research team will provide information regarding the study to the general public through social media platforms such as Twitter, Facebook, and Instagram etc. with use of marketing flyers (Attached as a separate

document). We will also directly contact several healthcare institutes including Premier Health Network (Dayton, Ohio) previously familiar with Heartfulness offerings through personal and professional contacts to inform about the study.

## **Informed Consent**

Subjects choosing to participate in the study will be sent the consent form via email, allowing them to review it. They can communicate via email where additional questions can be asked, and explanations will be provided. Secure Email communication will send and receive consent forms from subjects and limited to the study investigators. Wright State University has provided a designated secure email address: [[contact]](mailto:[contact]), to be used for communication with participants. Interested participants will be sent Wright State approved survey tool; Qualtrics web link & QR code. A consent form will be attached in Qualtrics with an electronic signature function for participants to be able to provide consent for the study. We will obtain primary demographic including age, gender, work designation, years of experience, level of education, primary patient population etc. (Please see attached Participant details form) and responses to the ProQOL, Work engagement scale through Wright State University approved survey tool; Qualtrics.

## **Measure**

The Professional Quality of Life Scale-5 (ProQOL-5) will be used to determine the risk for Compassion Fatigue (CF). ProQOL-5 uses 30 questions discretely separated into three subscales, assessing Compassion satisfaction (CS), Burn out (BO), and secondary traumatic stress (STS). The reliability of the ProQOL-5 is well documented and has established its reliability with previous research reporting a Cronbach's  $\alpha$  score ranging from 0.71 to 0.88. Cutoff scores of less than 43 (mild for STS/BO, severe for CS), 43 to 57 (moderate), and 57 or more (severe for STS/BO, mild for CS) were used for analysis. Cutoff scores for each participant will be calculated, and these scores will then be used to create risk profiles that show potential CF trends. Permission to use ProQOL-5 is obtained.

The Utrecht Work Engagement Scale (UWES) assesses levels of energy and mental resilience while working, along with a sense of significance, inspiration, pride, challenge, and concentration in work. Schaufeli and colleagues (2002) first proposed the UWES as a 17-item scale. Using exploratory factor analysis, they found three distinct factors of employee engagement: vigor, absorption, and dedication, consistent with their conceptualization.

All participants will be requested to provide testimonials or descriptive answers to the following qualitative questions in writing as a part of the survey at the end of 6 weeks, 3 months, and 6 months.

- Please describe how Heartfulness meditation or the Gratitude practice has impacted your general wellbeing (stress level, sleep quality)?
- Please describe changes in your interactions with family, friends, patients, or co-workers after joining the Heartfulness meditation program or the Gratitude practice program, i.e., feeling calmer, more empathetic, or compassionate, taking more time before reacting to a situation etc.
- Please describe if Heartfulness or the Gratitude practice has impacted your professional life in any way, i.e., better communication with patients or their family, improved focus on the assignment, less fatigue etc.
- Would you like to continue Heartfulness meditation practice or the Gratitude practice after the program ends?
- Please describe some of the challenges or difficulties faced to incorporate Heartfulness practice or the Gratitude practice in your daily routine and what were some ways you were or were not able to overcome them?
- Please suggest some ideas or feedback to improve or modify similar programs in future
- Please describe how you foresee Heartfulness practice or the Gratitude practice to be beneficial to you in future?
- How likely is it that you would recommend Heartfulness meditation practice or the Gratitude practice to a friend or family member? [Rated on a scale of 0-10; 0 - not at all likely through 10 extremely likely]

These data will be used for qualitative statistical analysis which will provide additional perspective to study results.

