- Video sessions will NOT be recorded to maintain the privacy of the participants.

- Educational sessions will be recorded in webinar mode without inclusion of participants, to be made available for participants to review later.
- Participants will be provided with an information sheet with detailed steps to join video conferences.
- Participants will be asked to enter the initials of their first and last name with their participant ID number and will be asked to keep their videos on during virtual sessions to promote friendly interaction with a trainer.
- Participants will not be allowed to share Zoom meeting identification numbers & passwords with anyone else either privately or will be allowed to post on any social media platform (included in the participants' consent form).

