### Certified Heartfulness Trainers

[name] (PI) is a physician and a certified Heartfulness trainer who will provide education, training and conduct all virtual meditation sessions during this study.

If any unforeseen situation forces an absence of [name], Co-Primary investigator: [name] will start a Video meeting (without video interaction between participants and trainer) and invite one of the alternate Heartfulness trainers ([name], [name], [name]) to maintain the privacy of the participants.

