### Data to be utilized

Participant Information from the Participant details form (attached)

Data from standardized assessment tools

From the Professional Quality of Life scale (attached)

From the Utrecht Work Engagement Scale (UWES)

Data will be extracted from the information collected from enrollment, assessment and classes and will be stored in a secured file only accessed by the PI.

Data analysis will include descriptive statistics, regression, and repeated measures ANOVA to assess the impact of any intervention on work engagement, compassion fatigue and burnout.

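### The principal investigator teaches the Heartfulness arm and alone opens the outcome file; separately, the survey's open questions lean towards benefit in both arms

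*Protocol*

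**What the plan says.** **Who teaches and who holds the data.** The protocol section Certified Heartfulness Trainers describes the PI as a "certified Heartfulness trainer who will provide education, training and conduct all virtual meditation sessions during this study". The section Data to be utilized says that information from enrolment, assessment and classes "will be stored in a secured file only accessed by the PI". In the section Heartfulness meditation group, participants enter their initials "with their participant ID number and will be asked to keep their videos on during virtual sessions". The Objectives describe the Gratitude practice as self-motivated. The section Gratitude practice group gives it one orientation, a weekly reminder email and weekly podcast access.

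**What the survey asks.** The Measure section sets out the two scales, ProQOL-5 and UWES, and then a list of open questions for 6 weeks, 3 months and 6 months: "All participants will be requested to provide testimonials or descriptive answers to the following qualitative questions in writing as a part of the survey". One item reads "Please describe how you foresee Heartfulness practice or the Gratitude practice to be beneficial to you in future". Two others illustrate the answer only with favourable examples: "feeling calmer, more empathetic, or compassionate, taking more time before reacting to a situation etc" and "better communication with patients or their family, improved focus on the assignment, less fatigue etc". Another item goes the other way: "Please describe some of the challenges or difficulties faced to incorporate Heartfulness practice or the Gratitude practice in your daily routine". The section says that these answers will add perspective to the study results.

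**Safeguard.** Research Materials, Records and Confidentiality says that identifying details are replaced by a survey identification number.

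**The concern.** Participants cannot be blinded to which practice they follow, and ProQOL-5 and UWES are self-reports. In that setting the main remaining protection is distance between the person who delivers an intervention and the person who receives and handles its outcomes. The protocol removes that distance in one arm only. Heartfulness participants may meet the PI several times a week, and the PI then has sole access to their scores. Gratitude participants have no comparable contact in the text. If Heartfulness participants answer more warmly for that reason, the shift adds directly to the estimated difference, and no later analysis can separate it from an effect of meditation. Sole access also means that no second, uninvolved person sees the data while they are being extracted.

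The open questions raise a different issue. A request for testimonials, together with leading items, draws favourable text from both arms. The qualitative findings would then look more positive for both practices than neutral questions would make them.

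**Working it through.** The protocol gives no significance level, power, effect size or standard deviation, so there is no figure of its own to reproduce. The check is mainly a comparison of sections.

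**1. Contact and custody by arm**

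| | Heartfulness | Gratitude |
|---|---|---|
| PI's teaching role | conducts all sessions | none stated |
| Live sessions | offered daily; at least two morning and two evening sessions a week requested | one orientation |
| Seen by the PI | initials and participant ID shown, video requested | not described |
| Who opens the data | PI only | PI only |

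The last row is the same for both arms. The asymmetry comes from combining it with the first three.

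**2. Count of the eight open questions**

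- Presumes benefit: 1 (future benefit).
- Gives only favourable examples: 2 (interactions with others; professional life, although this one asks whether there was any impact).
- Neutral or open to criticism: 5 (wellbeing, wish to continue, difficulties, suggestions, 0-10 recommendation).

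So 3 of 8 lean favourable. Seven of the eight name both practices; the request for suggestions names neither. The wording is the same in both arms.

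**3. Can an answer be tied to one practice?**

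- At 6 weeks: largely yes. Study design releases both sets of material only at the end of 6 weeks, so the known allocation identifies the practice.
- At 3 and 6 months: less clearly, because everyone then holds both sets. The section Gratitude practice group limits this for controls, who complete the ProQOL-5 at those times unless they have started Heartfulness.

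**4. Illustration of size (assumptions only)**

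Suppose there is no true effect, outcomes have SD 1, the planned 200 and 100 are all analysed without covariate adjustment, and the test is two-sided at 5%. A reporting shift of b SD occurs in the Heartfulness arm only.

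SE = sqrt(1/200 + 1/100) = sqrt(0.015) = 0.1225

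Rejection rate = 1 − Φ(1.96 − b/SE) + Φ(−1.96 − b/SE)

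| b (SD) | b/SE | Rejection rate |
|---|---|---|
| 0 | 0 | 5.0% |
| 0.1 | 0.82 | 12.9% |
| 0.2 | 1.63 | 37.2% |
| 0.3 | 2.45 | 68.8% |

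A second setting, with 100 and 80 completers and adjustment for a baseline correlation of 0.6 (all assumed), gives SE = sqrt((1 − 0.36) × (1/100 + 1/80)) = sqrt(0.0144) = 0.12. Shifts of 0.1 and 0.2 SD are then 0.8 and 1.7 standard errors, so the picture hardly depends on which setting is used. Neither calculation says that a shift of this size will occur, and neither assigns a share of it to file access.

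**The case against.** There is a good deal to be said for the plan as written, and much of it stands.

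- *Identical prompts cannot favour one arm.* This stands. A reader might infer that the leading questions themselves bias the comparison towards Heartfulness. The protocol puts the same wording to everyone, so any imbalance must come from the PI's contact with one arm and custody of the data.
- *The open questions are supplementary and mostly balanced.* This stands. A reader might infer that the qualitative results could never show a lack of benefit. But participants may report difficulties, decline to continue, or give a rating of 0. The tilt is partial.
- *Spill-over onto the scales is not shown.* This stands. The order of items is not given, and the Measure section describes the scales first.
- *Answers go into a university Qualtrics survey, and names are replaced by a number.* This stands in part. A reader might infer that the PI can match answers to faces. The protocol speaks of a participant ID in sessions and a survey identification number for the forms, and does not say that they are the same. Video is only requested, and home practice may replace guided sessions. Still, names and email addresses are verified before sessions, and enrolment, assessment and class data share one PI-only file, so the text states no barrier between trainer and answers.
- *What participants believe about who reads their answers may be covered in the consent form.* This stands: that form is not shown, so its silence cannot be assumed.
- *The 3- and 6-month answers cannot be attributed at all.* A reader might infer this too, but it goes too far, given the provision for controls who start Heartfulness.

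None of this answers the central point. The person who teaches one arm is the only one with access to the outcomes of both.

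**Conclusion.** The point holds in two separate parts.

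First, a PI who teaches only in the Heartfulness arm, so far as the protocol states, has sole access to unblinded, self-reported outcomes. This creates a credible risk of more favourable reporting or handling in that arm. The structural asymmetry is documented; the behavioural consequence is an inference, and its size is unknown. The 13% and 37% error rates above rest wholly on assumed shifts of 0.1 and 0.2 SD.

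Second, and in both arms equally, the request for testimonials and three of eight leading items tilt the supplementary qualitative results towards benefit. Naming both practices makes the later answers harder to attribute.

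Neither part invalidates the randomised comparison. Both are worth correcting because the correction is cheap and a reporting shift cannot be removed after collection.

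**What to change.** 1. **Data to be utilized:** have an existing co-investigator who does not teach hold the outcome file. The co-primary investigator is a natural candidate, since Certified Heartfulness Trainers gives that person the task of bringing in alternate trainers rather than teaching. Give the PI only coded data, after collection closes, and tell participants that their trainer does not see their answers.
2. **Measure, open questions:** delete the request for testimonials. Replace the three leading items with neutral ones, for example: *Describe any change you have noticed since starting your assigned practice, whether better, worse or none.* Use survey branching so that each participant sees only the name of the assigned practice.
3. **Measure:** state that ProQOL-5 and UWES are completed before the open questions appear. This settles something the protocol leaves open and may already be the intention.

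The cost is some Qualtrics wording and ordering, a small change in file permissions within the existing team, and fewer quotable testimonials. The interventions and sample size do not change. The fix does not remove the bias that any unblinded self-report can carry; it removes the part that custody and wording could add.
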